# An individually tailored family-centered intervention for pediatric obesity in primary care: study protocol of a randomized type II hybrid effectiveness–implementation trial (Raising Healthy Children study)

**DOI:** 10.1186/s13012-017-0697-2

**Published:** 2018-01-15

**Keywords:** Family Check-Up 4 Health, Primary care, Hybrid effectiveness–implementation trial, Pediatric obesity, Integrated care, Coordinated care

## Abstract

**Background:**

Pediatric obesity is a multi-faceted public health concern that can lead to cardiovascular diseases, cancers, and early mortality. Small changes in diet, physical activity, or BMI can significantly reduce the possibility of developing cardiometabolic risk factors. Family-based behavioral interventions are an underutilized, evidence-based approach that have been found to significantly prevent excess weight gain and obesity in children and adolescents. Poor program availability, low participation rates, and non-adherence are noted barriers to positive outcomes. Effective interventions for pediatric obesity in primary care are hampered by low family functioning, motivation, and adherence to recommendations.

**Methods:**

This (type II) hybrid effectiveness–implementation randomized trial tests the Family Check-Up 4 Health (FCU4Health) program, which was designed to target health behavior change in children by improving family management practices and parenting skills, with the goal of preventing obesity and excess weight gain. The FCU4Health is assessment driven to tailor services and increase parent motivation. A sample of 350 families with children aged 6 to 12 years who are identified as overweight or obese (BMI ≥ 85th percentile for age and gender) will be enrolled at three primary care clinics [two Federally Qualified Healthcare Centers (FQHCs) and a children’s hospital]. All clinics serve predominantly Medicaid patients and a large ethnic minority population, including Latinos, African Americans, and American Indians who face disparities in obesity, cardiometabolic risk, and access to care. The FCU4Health will be coordinated with usual care, using two different delivery strategies: an embedded approach for the two FQHCs and a referral model for the hospital-based clinic. To assess program effectiveness (BMI, body composition, child health behaviors, parenting, and utilization of support services) and implementation outcomes (such outcomes as acceptability, adoption, feasibility, appropriateness, fidelity, and cost), we use a multi-method and multi-informant assessment strategy including electronic health record data, behavioral observation, questionnaires, interviews, and cost capture methods.

**Discussion:**

This study has the potential to prevent excess weight gain, obesity, and health disparities in children by establishing the effectiveness of the FCU4Health and collecting information critical for healthcare decision makers to support sustainable implementation of family-based programs in primary care.

**Trial registration:**

NCT03013309 ClinicalTrials.gov

**Electronic supplementary material:**

The online version of this article (10.1186/s13012-017-0697-2) contains supplementary material, which is available to authorized users.

## Background

Childhood obesity has become the leading preventable cause of death worldwide [1]. Poor diet/nutrition and physical inactivity are the leading and preventable contributors to obesity and are among the principal causes of chronic disease and mortality for youths [2]. Obesity is also related to psychosocial issues in youth, such as depression and academic disengagement [3–5]. In the USA in 2013–2014, it was estimated that 18% of all 6–11-year-old children were obese and that a disproportionate number are disadvantaged economically and socially [6]. Obesity and its health consequences are disproportionately distributed across the USA; Mexican Americans, American Indians, and African Americans have the highest prevalence rates of obesity in childhood at 41.1 to 56.3% [6–9]. Social determinants of health [10] play a key role in the childhood obesity and contribute substantially to disparities. In the social environment, stress and discrimination are acutely experienced by minority and low-income communities in the USA and are linked with childhood obesity [11]. Physical environment barriers include limited access to safe areas for play and fresh, nutritious foods [12]. Finally, access to health services that can prevent obesity and its sequelae [13] is limited for members of underserved groups [14].

While addressing the social determinants of health is an ongoing task, significant evidence supports the effectiveness of lifestyle modification on cardiometabolic risk factors, with even small changes yielding significant impact [15]. Recently published reviews [16, 17] indicate that youth health behaviors and obesity may be improved when parents attend and are directly involved with services [18] and are provided training in the skills required to support lifestyle modification in accordance with expert guidelines [16, 19–21].

Primary care is a promising context for improving parenting behaviors linked to child health [22–24]. Most children access a primary care provider annually [25, 26], caregivers are present at visits, and physicians have a high level of perceived authority among parents who look to them for advice on children’s health. The National Academy of Medicine, the American Academy of Pediatrics, and the Endocrine Society, among others, promote a family-centered intervention in primary care [27–29]. Despite the appeal of a family-centered approach [30, 31], several barriers hinder implementation of such programs in real-world healthcare systems [29, 32]. For example, healthcare providers report inadequate time, training, and resources to effectively work with parents to address childhood obesity [33]. Few comprehensive and prospective evaluations of the implementation of weight management programs in primary care have been done, despite such factors as inadequate cost evaluation being a top reason for failure to adopt behavioral interventions [34] and the general concern about delivery with sufficient fidelity to preserve effectiveness [35]. To have a population impact on pediatric obesity, there is a pressing need for scalable programs that can be delivered in primary care and engage parents in behavior change strategies for children [32].

### The Family Check-Up for Health program

The Family Check-Up 4 Health (FCU4Health) is an adaptation and enhancement of the original Family Check-Up (FCU), an evidence-based, family-centered intervention with empirical evidence of effectiveness and feasible delivery in real-world systems that provide care for culturally diverse, low-income families [36–39]. Initially designed and tested as a behavioral health intervention, the FCU employs motivational interviewing (MI) to engage parents in family management strategies and community-based support services [40]. Extensive data document the FCU’s clinical effectiveness and high rates of engagement among underserved and ethnic minority families [36–38, 41–43]. Although not targeted by the program, the FCU demonstrated long-term collateral effects on nutrition (ages 2–5) and obesity (ages 2 to 10 years) [44] and on those from adolescence to early adulthood (ages 12 to 22 years) [13, 44]. Improvement in parent–child relationships and positive behavior support mediated the effects of the FCU on nutrition and obesity in both developmental periods. Based on these findings, the FCU4Health was developed to specifically target pediatric obesity in primary care, the front-line service setting for prevention of obesity and excess weight gain [29]. This involved enhancing the content to focus on helping parents support child and family behaviors that lead to a healthy weight, and adapting the delivery strategy for the primary care context (Smith JD, Berkel C, Rudo-Stern J, Montaño Z, Mauricio AM, Dishion TJ, St. George SM, Prado G, Chiapa A, Bruening MM, The Family Check-Up 4 Health (FCU4Health): The process of adapting an evidence-based parenting program for prevention of pediatric obesity and excess weight gain in primary care, submitted).

The FCU4Health is unique relative to other obesity interventions in that rather than solely targeting *knowledge* about national health guidelines (published by such organizations as the American Academy of Pediatrics and United States Department of Agriculture that require updating over time), it provides parents with the *skills and support* to implement the changes recommended by physicians, dieticians, and other members of the healthcare team. This aspect fills an important gap for families who earnestly agree to improve children’s diet, physical activity, sleep habits, or screen time while in the clinic but encounter difficulties in their regular involvement that lead to an abandonment of these efforts. It also increases the individualizability of the intervention to the needs of the family and reduces training time and the need for regular updates to program materials.

The core components of the FCU4Health mirror those of the original FCU: an ecological assessment of the family, a feedback and motivation session, and follow-up services that are individually tailored in content and dosage based on identified needs in the assessment (see Fig. 1). These follow-up services may include parenting modules for needs related to family management and/or care coordination with community-based services to address ecological needs [38]. Parenting modules follow *Everyday Parenting*, [45] a 12-module skills-based curriculum focusing on the three core areas of parenting and family management: relationship quality, positive behavior support, and monitoring and limit setting. The application of these steps in this trial is described in greater detail in the “Methods” section.

**Fig. 1 Fig1:**
[figure not shown]
Steps and elements of the Family Check-Up for Health (FCU4Health) program in the Raising Healthy Children study

### Study design

#### Overview

We will test the FCU4Healtth with a type II hybrid effectiveness–implementation trial [46], which enables simultaneous evaluation of the clinical effectiveness and the delivery of the FCU4Health program using two different implementation strategies [47].

#### Implementation strategies and service delivery sites

The delivery model used by a given practice depends upon their programmatic, fiscal, and resource characteristics and needs [48]. Several approaches for the delivery of behavioral health services in primary care settings have been described [49]. In this trial, we partnered with three pediatric primary care agencies that serve high rates of low-income, ethnic minority families (about 60–65% Latino; 10% African American; 5–8% American Indian). Because pediatric primary care offices often do not have integrated behavioral health, arm 1 uses a strategy of coordinated care between primary care and an external behavioral health provider. We partnered with a large outpatient general pediatrics clinic associated with a children’s hospital. We also partnered with two agencies that are part of the nationwide network of 1250 Federally Qualified Health Centers (FQHCs). A feature of FQHCs is the integrated care model that typifies the medical home. In arm 2, we will test an integrated/co-located model of care. The FQHC network is crucial for embedding a family-centered approach to care because it serves youth and families at high sociodemographic risk and is intended to integrate services to reduce barriers and improve care. Partnering with these provider sites afforded the opportunity to compare FCU4Health implementation under two different real-life service delivery models. In both arms, behavioral health consultants are responsible for delivering the FCU4Health and coordinating care with other support services and resources.

#### Clinical effectiveness of the FCU4Health

Within the two implementation strategy arms, eligible families are randomized to receive either the FCU4Health or clinic services-as-usual plus community program information (see “Methods”). Primary clinical outcomes are child BMI and body composition. Secondary outcomes, hypothesized to mediate effects of the intervention on primary outcomes, are lifestyle behaviors (diet and nutrition, physical and sedentary activity, sleep), child self-regulation, and family management practices.

## Methods

### Study aims

#### Aim 1

Aim 1 was to finalize the adaptation of the FCU4Health, which was initially adapted and piloted in pediatric primary healthcare [50], based on input from a community advisory board (CAB) and partner clinics.

#### Aim 2

Aims 2 was to evaluate the effects of two delivery strategies: integrated/co-located care and coordinated care with referral. Using a mixed-methods approach applied to Proctor et al.’s [51, 52] taxonomy, we will evaluate the process of implementing the FCU4Health to inform, taking the program to scale.2a. Evaluate fidelity over time to the FCU4Health using a validated observational rating system [53–55] and develop and test an automated fidelity coding system [56].2b. Employ behavioral intervention costing methods [57] to evaluate the costs of installing and delivering the FCU4Health and conduct a cost–benefit analysis to evaluate the monetary benefits of program effects.2c. Develop a plan to support scale-up and sustainment in collaboration with our CAB.

#### Aim 3

Aim 3 was to use pragmatic trial principles to test program effects on primary and secondary outcomes. Intervention effects on proximal outcomes will be tested as mediators on the distal outcomes of child BMI and body composition.

#### Aim 4

Aim 4 was to carefully track utilization in each aspect of the program, gather data concerning family’s service delivery preferences and satisfaction, and test a model of program implementation where family engagement mediates the relation between fidelity and clinical outcomes [58].

### Study participants, recruitment, and randomization

Families with children 5.5 to 12 years of age with BMI ≥ 85th percentile for age and gender at study entry are eligible to participate. Participants will be identified during clinic well- and sick-child visits and through queries of the Electronic Health Record (EHR). Enrolled families will complete an ecological, family health routine assessment. After the first assessment, families will be randomly assigned to the FCU4Health (*n* = 200) or Services-as-Usual Plus Information condition (*n* = 150) using a stratified block randomized design by child gender, age, language (English, Spanish), and ethnicity. Assessing the family prior to randomization ensures double-blinding at baseline. Families in the intervention condition will participate in the FCU4Health program, as outlined in the next section, in addition to receiving usual care through their clinic. Families are compensated for completing assessments, but not for engaging in services. A CONSORT table is presented in Fig. 2.

**Fig. 2 Fig2:**
[figure not shown]
CONSORT flow diagram

### Family Check-Up 4 Health program

#### Delivery schedule

Previously, the FCU has used a health maintenance approach, in which parents receive periodic (annual) FCUs [38, 59]. Based on the US Preventive Services Task Force recommendations that overweight/obese youth should be provided with at least moderate treatment dosage to affect weight management [60], we designed a delivery schedule to achieve a minimum *targeted* dose of intervention between 25 and 50 h over 6 months (assessment and feedback at months 1, 3, and 6). Because of the tailored approach, families with greater need and those with greater motivation are expected to participate in more follow-up services [61].

#### FCU4Health family health routine assessment

The family health routine assessment is ecological and evaluates five broad domains—family health behaviors, child health behaviors, family well-being and support, child adjustment, and family management and relationships—using a multi-agent battery of caregiver- and child-reported questionnaires and a series of brief video-recorded family interaction tasks (FITs). Two versions of the assessment are used in this study: a full version at months 1, 6, and 12 (90 min to complete) and a brief version administered only at the 3-month assessment (30 min). The full version includes all questionnaires across the five broad domains and three FITs on the topics of health and diet goals, monitoring and limit setting of child health behaviors, and planning a fun physically active family activity (4 min each). The brief version includes only the questionnaires to caregiver and child pertaining to family health behaviors and child health behaviors and is intended as a low-burden opportunity to reinforce steps toward behavior change and address areas that have not yet improved or potentially shift focus to areas that have emerged during the first 3 months of intervention. Questionnaires are completed in English or in Spanish by caregivers and the child through a secure website accessed via a Wi-Fi enabled tablet. Pencil-and-paper versions are available if needed. FITs are recorded using the tablet and are uploaded to a cloud-based, HIPAA-compliant portal for secure storage, viewing, and scoring.

#### Feedback sessions

Feedback sessions follow the assessments in months 1, 3, and 6. The first feedback session begins with a discussion to understand (a) the caregivers’ perception of their needs; (b) their child’s health, adjustment, and obesogenic behaviors; and (c) the caregivers’ motivation to change parenting and family management practices in support of health behavior change. In the second and third feedbacks, the coordinator begins by checking in with the family about their progress, discussing barriers they are experiencing, and exploring the ways that the previous feedback and *Everyday Parenting* sessions were helpful for them in catalyzing and supporting healthy lifestyle behavior change. The coordinator presents the findings of the family health routine assessment using the Feedback Form, which summarizes where families are in the five areas of the assessment relative to age-based norms with a stoplight color scheme. Family strengths are represented in green, yellow indicates areas to monitor, and red accentuates areas in need of further support. The goals of this session are to (a) share assessment findings with family members regarding strengths and challenges, (b) engage in a motivation-enhancing discussion about promoting positive changes, and (c) provide a menu of resources and next steps for intervention. The first two feedback sessions lay out a plan for the follow-up services (i.e., *Everyday Parenting* sessions or referrals to community-based services) and use MI techniques to increase buy-in for the planned course of action. In the final feedback session (month 6), feedback and motivation focus on the progress the family has made and continuing engagement in community services to address areas in need of additional support.

#### *Everyday Parenting* sessions

In the FCU4Health, *Everyday Parenting* sessions are tailored to the family’s specific needs identified in the family health routine assessment and focus on a specific behavior change goal, such as setting limits on snacking between family meals or monitoring children’s sedentary and physical activity time. It is expected that families will engage in 8–16 sessions of *Everyday Parenting* over the 6-month intervention period. The focus is on supporting and maintaining children’s healthy behaviors. It is also expected that during these sessions, the FCU4Health coordinator will help the caregivers problem-solve challenges they have encountered in implementing recommended health behavior changes.

#### Community programs and support services

To address needs related to health behaviors (e.g., nutrition and physical activity programs), specialty medical needs (e.g., asthma, diabetes), and the social determinants of health that affect parents’ ability to support child health (e.g., employment, food and housing insecurity, insurance coverage), coordinators provide families with referrals to existing resources in the community. We will identify programs in collaboration with our partner agencies that are available at little or no cost to families. The intent is to leverage existing services to support families and to test whether the motivational aspects of the FCU4Health lead to increased engagement compared to families in usual care. A centralized repository of available programs and their requirements is stored in a Web-based hub, which can be updated by coordinators and other staff.

#### Phone-based coaching

In weeks where a face-to-face session is not scheduled or does not occur (e.g., cancelation, no show), the coordinator or a behavioral health support staff person (e.g., a community health worker) conducts a 15- to 30-min phone-based coaching session. The purpose is to maintain contact with the family and help problem-solve challenges, reinforce positive achievements, and continually address motivation to change and barriers to engagement. Additional information about the program is available in the FCU4Health protocol manual [62].

### Services-as-Usual Plus Information condition

Families randomized to the services-as-usual arm will receive care as usual from their primary care provider and any additional services offered by the agency, as well as a listing of the same community resources offered to families randomized to the FCU4Health arm.

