*Cost* data collection is multi-method in order to perform analyses from multiple perspectives (e.g., agency, payor, family). Study staff report activities weekly on an electronically administered survey. FCU4Health coordinators complete a brief survey after each contact with study families (in the intervention arm) to capture the staff involved and the number of hours spent. Electronic budgets track program spending and will be used to prospectively separate costs associated with implementation from those specifically related to research (e.g., participant reimbursement, data analysis software), start-up (e.g., training), and ongoing costs (e.g., consultation with FCU4Health developers, technical assistance, travel for home visitation). At each assessment, families will be asked to provide a release for the study team to obtain health plan claims data, which will be used to identify relevant health services utilization and associated costs.

Critical to the study’s implementation aims, such as the calculation of reach and cost, is the careful tracking of participation in the various components of the program. Using methods developed and tested in previous trials, the FCU4Health coordinators and other agency staff will track all family contacts and record the delivery location, travel time, details of participating family members, the type of the FCU4Health session, content areas covered, and referrals. At each assessment, caregivers will report on their engagement in community resources, how well these resources met their needs, and the amount of time spent in activities to support health child and family behaviors.

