Baseline weight, ecological risk, minority status, poverty status, and child gender will be included as covariates and tested as potential moderators. Moderation of program effects will be examined by adding a program by moderator interaction in the models of primary outcomes and mediators one at a time. For significant interactions, post hoc probing of simple effects (i.e., effects at different values of the moderator) will be conducted, following Aiken and West [105]. Accounting for the imperfect reliability, we have power to detect moderation effects that account for *R*^2^ ≤ 3% of the outcome [106].

We will examine whether it is necessary to account for site and coordinator effects by calculating the design effect metric [107]. If significant, we will modify our statistical plans and utilize multi-level models with site or coordinator as the cluster variable.

#### Aim 4

To determine differences in family participation between conditions, we will use the Wilcoxon rank-sum tests. We have sufficient power to detect a medium effect for this analysis (*f* ≥ .30). Next, we will use path analysis in structural equation modeling to test a model of program implementation where family engagement mediates the relation between fidelity and clinical outcomes [58]. Using automated fidelity data on the FCU4Health condition sample (*N* = 200), we have power to detect a mediated effect if the two paths each has a small-to-medium effect (*β* values ≥ .21).

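### Control contact with FCU4Health-trained staff is possible at the co-located clinics, but no described source would clearly identify it, and delivery strategy is missing from the moderator list

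*Protocol article*

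**What the plan says.** All references are to the protocol article.

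- **Randomisation** (Clinical effectiveness of the FCU4Health) is by family: "Within the two implementation strategy arms, eligible families are randomized to receive either the FCU4Health or clinic services-as-usual plus community program information". Both conditions are therefore recruited from the same clinics.
- **Control condition** (Services-as-Usual Plus Information condition): these families "will receive care as usual from their primary care provider and any additional services offered by the agency", plus a list of the community resources offered to the other condition. No agency service is excluded.
- **Who delivers the programme** (Implementation strategies and service delivery sites): "In both arms, behavioral health consultants are responsible for delivering the FCU4Health and coordinating care with other support services and resources". Here the arms are delivery strategies. For the hospital clinic, "arm 1 uses a strategy of coordinated care between primary care and an external behavioral health provider"; for the two health centres, "In arm 2, we will test an integrated/co-located model of care". Under Phone-based coaching, support staff such as community health workers may also have programme contact.
- **Contact records** (Measures, Implementation): "FCU4Health coordinators complete a brief survey after each contact with study families (in the intervention arm". The next paragraph has coordinators and other agency staff tracking family contacts, with no condition named.
- **Moderators** (Data analysis, Aim 3): "Baseline weight, ecological risk, minority status, poverty status, and child gender will be included as covariates and tested as potential moderators". Site enters only through a design-effect check.
- **Use of control data**: the Data analysis overview assigns it to aims 2b and 3. Aim 4 then compares family participation between conditions.

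**The concern.** An open-ended control condition, shared clinics and co-located delivery staff together leave a route by which control families could meet staff trained in FCU4Health. Whatever reached controls this way would pull the pooled BMI contrast towards zero. A weak result would then be hard to read: the programme may not work, or the comparator may have received part of it. A record of who saw control families would help to separate these explanations.

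The same sentence on usual care may also mean different things at the two kinds of site. A health centre with integrated behavioral health may offer more than a clinic that relies on an external provider. Comparing FCU4Health under two real-life service models is a stated purpose, so a reader will want the effect within each strategy, set beside what controls there actually used. The moderator list does not provide for this.

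**Working it through.** **1. Would the described sources show control contact with trained staff?**

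| Source | Covers controls? | Identifies trained staff or programme content? |
|---|---|---|
| Coordinators' post-contact survey | No: "complete a brief survey after each contact with study families (in the intervention arm" | Yes, staff involved and hours |
| Contact tracking by coordinators and agency staff | Not stated; introduced as tracking participation in programme components, and its fields include the type of FCU4Health session | Yes, if controls are in scope |
| CREA caregiver survey | No restriction by condition | Not described; records engagement (including mental healthcare) and whether help worked |
| DECR caregiver survey | No restriction by condition | Not described; records frequency and duration |
| Health plan claims | No restriction by condition, but needs a family release | Not described; used for service utilisation and costs |
| Aim 4 comparison of participation | Yes, if conditions means FCU4Health versus usual care | Not described |

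The last row needs care. The Discussion also uses the word condition for a delivery strategy. Read as the randomised conditions, Aim 4 uses control data that the overview assigns only to aims 2b and 3.

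**2. The plan's own figure.** Aim 3 states d ≥ .25 for ANCOVA with 200 v 150. The overview gives power .80 and two-sided α = .05.

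- Unadjusted standard error: √(1/150 + 1/200) = .1080. Detectable d: (1.960 + .842) × .1080 = .303.
- ANCOVA multiplies this by √(1 − ρ²), where ρ is the baseline–outcome correlation. Reaching .25 needs ρ ≈ .56 with no attrition, or .62 to .65 at the stated 10 to 15% attrition.
- The article gives no ρ, so the figure can be neither confirmed nor called wrong. It is taken as given below. No allowance for contamination is mentioned.

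**3. Dilution, as illustration only.** Let s be the share of controls at the health centres, c the share of those exposed, and k the fraction of the programme effect conveyed. All three are assumptions. The effect is multiplied by f = 1 − s·c·k. With 80% power at d = .25, power is Φ(2.802·f − 1.960).

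| Assumptions | c = 10% | c = 20% | c = 30% |
|---|---|---|---|
| s = 2/3, k = 1: f | .933 | .867 | .800 |
| s = 2/3, k = 1: power | 74% | 68% | 61% |
| s = 1/2, k = 1: power | 76% | 71% | 66% |
| s = 2/3, k = 1/2: power | 77% | 74% | 71% |

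With an unadjusted t test, true d = .30, s = 2/3 and k = 1, d becomes .28, .26 or .24, and power falls from 79% to 73%, 67% or 60%. At d = .50, the size Aim 3 cites for family-centered programmes, the 30% case leaves .40 and about 96% power.

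**4. Precision of condition × strategy.** Assume two thirds of each condition is at the health centres: 133 v 100 there and 67 v 50 at the hospital clinic.

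- Standard errors of the two contrasts: √(1/133.3 + 1/100) = .132 and √(1/66.7 + 1/50) = .187.
- Standard error of their difference: √(.0175 + .0350) = .229. The 95% interval is ±1.96 × .229 = ±.45 unadjusted.
- Scaled to the plan's stated precision (.25/.303 = .826), it is about ±.37.

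The estimate would be imprecise, which is why it should be labelled exploratory.

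**The case against.** A reader might infer that contacts are recorded only for intervention families and that contamination would therefore be invisible. The article does not support that. The restricted survey belongs to the cost measures. The separate tracking sentence names no condition. Caregiver reports and claims cover service use without restriction by condition, and use of support services is an Aim 3 outcome. Usual care at each type of site can therefore be described. What remains is narrower: no source is clearly described as showing who saw a control family or whether programme content was given.

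A reader might also infer that contamination does occur. It is only possible. No sentence says that trained staff see control families, and incidental contact is far from a targeted 25 to 50 hours over six months. The dilution figures with k = 1 are accordingly an upper bound for each assumed exposure rate.

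Usual care that differs between clinics is legitimate in a pragmatic trial, and each within-strategy contrast is valid against local usual care. No planned analysis attributes a BMI difference to the embedded model. Strategy is not randomised and is tied to clinic type across three sites, so an interaction cannot isolate it. All of this stands, and it limits how the estimate may be read. It does not remove the value of showing it.

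Finally, staff assignment and contamination safeguards may be set out in the full protocol or manual, so their absence from an article is not held against the plan. The limit on the survey and the explicit moderator list, by contrast, are written choices.

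**Conclusion.** The point holds in a limited form. Control contact with FCU4Health-trained staff is possible under the stated design, the one instrument that clearly records such contact is confined to intervention families, and the scope of the wider tracking is unclear. Delivery strategy is absent from the moderator list although it defines the groups within which families are randomised.

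The size is unknown because the document gives neither the split of families between clinics nor any exposure rate. Under the assumptions shown, power at d = .25 falls from 80% to between 77% and 61%; with the large effect cited for family-centered programmes, little would be lost. It does not follow that the trial is underpowered, that its detectable difference is wrong, or that the comparator is contaminated. The value of the change lies in being able to interpret a small or null effect, and in letting the effect under each strategy be read against the care that controls received there.

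**What to change.** 1. **Record.** Extend the existing post-contact survey to any contact that a trained coordinator or support worker has with a services-as-usual family, and state which families the wider contact tracking covers. Report control exposure, and CREA and claims service use, by delivery strategy beside the intent-to-treat result. A complier-average sensitivity estimate is optional.
2. **Analyse.** Add delivery strategy as a covariate, and condition × strategy to the Aim 3 moderator list. Report an estimate with its confidence interval, labelled exploratory, noting that strategy is not randomised and is confounded with clinic type.
3. **Reconcile.** Align the overview's statement on the use of control data with the Aim 4 comparison, and say there whether conditions means the randomised groups or the delivery strategies.

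The cost is a few more entries in an electronic survey that staff already complete, one extra model and some clarified wording. Recruitment was in progress when the article was submitted. Contacts not logged as they occur may be hard to recover, so the survey change is the more urgent. Nothing here alters what care either group may receive.
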